# Efficacy and safety of acupuncture for hand osteoarthritis: study protocol for a multi-center, randomized, sham-controlled clinical trial

**DOI:** 10.1186/s13018-023-03570-6

**Published:** 2023-02-06

**Keywords:** Acupuncture, Hand osteoarthritis, Clinical trial, Efficacy and safety

## Abstract

**Background:**

Hand osteoarthritis (OA) is a prevalent disorder in the general population. Patients with hand OA often report symptoms of pain, stiffness, and functional limitations, which cause clinical burden and impact on quality of daily life. However, the efficacy of current therapies for hand OA is limited. Other therapies with better effects and less adverse events are in urgent need. Acupuncture is well known for analgesia and has been proved effective in treating basal thumb joint arthritis. This study aims to clarify the efficacy and safety of acupuncture treatment for clinical symptomatic improvement of hand OA.

**Methods:**

This will be a sham-controlled, randomized, multi-center clinical trial. A total of 340 participants will be recruited and randomly allocated to either traditional acupuncture group or sham acupuncture group. All participants will receive 12 treatment sessions over 4 weeks and 2 follow-up assessments in the following 3 months at week 8 and week 16. The primary outcome will be the proportion of responders at week 5. Secondary outcomes will include visual analog scale, Australian Canadian Osteoarthritis Hand Index, Functional Index for hand OA, the number of symptomatic joints, hand grip strength and pinch strength, global assessment, the World Health Organization Quality of Life abbreviated version and expectations. Safety will be evaluated during the whole process of the trial. All outcomes will be analyzed following the intention-to-treat principle.

**Discussion:**

This prospective trial will provide high-quality evidence on evaluating the efficacy and safety of acupuncture treatment for hand OA. Results of this trial might contribute in offering a new option to clinical recommendations.

*Trial registration* ClinicalTrials.gov Identifier: NCT05267093. Registered 23 February 2022.

## Introduction

Hand osteoarthritis (OA) is a common disorder causing disabling pain, stiffness, reduced grip and/or pinch force and loss of motion [1–3]. The overall prevalence of hand OA was estimated to be 8.99–12% around the world [3–5]. Symptomatic hand OA is more frequently seen in the elder population, and the prevalence in women is twice higher than in men [6, 7]. Radiographic features such as joint space narrowing, osteophyte formation, and subchondral sclerosis are usually identified by plain radiography [2]. Hand OA can affect single or multiple joints, and the dominant hand is more likely to be affected due to over usage [8]. Risk factors consist of age, joint hypermobility, trauma, inflammation and gene locus related to cartilage calcification, which contribute complicatedly to the etiology and aid the change of joint structure [1, 2, 8–10]. Therefore, hand OA is a heterogeneous disorder that is hard to predict.

At present, no disease-modifying treatment is available to cure hand OA by reducing pain and improving joint motion [11]. Out of safety reasons, the first-line choice for hand OA treatment is topical pharmacologic intervention rather than oral medicine [11, 12]. It is reported that topical non-steroidal anti-inflammatory drugs (NSAIDs) have significant positive effect for hand OA after 4-week treatment [13]. However, the long-term effect is not clear [11, 14], and the difference between topical pharmacologic intervention and placebo are still in argument [15]. Although considered much safer than systematic drugs, the topical drugs require additional caution in use because it may result in skin adverse effects (AEs) with prevalence of 10–39% [16, 17]. Other available therapies, such as intra-articular steroids, oral chondroitin sulfate and dietary supplements, fail to provide certain benefit to patients with hand OA. Thus, alternative therapies with better effect and less AEs are considerably in need.

Acupuncture is an ancient non-pharmacologic therapy derived from traditional Chinese medicine and is well known for analgesia. Acupuncture has been proved an effective therapy for knee OA [18, 19], whereas, evidence on its efficacy for hand OA is extremely limited. Symptoms of hand OA are similar to those of knee osteoarthritis, including pain, loss of function and change in joint structure. Also, both knee and hand OA share similar pathophysiology of degradation of the cartilaginous matrix [1, 20]. Recent studies reported that acupuncture alleviates pain in knee OA by regulating inflammation and inhibiting hypertrophic differentiation [21], which has proved the efficacy of acupuncture treatment to osteoarthritis. Hence, acupuncture may be a promising alternative therapy for hand OA. Barnard et al. [22] reported a randomized controlled trial with 70 basal thumb joint arthritis patients comparing acupuncture and sham acupuncture (35/35). Both groups showed significant post-treatment improvement in pain relief, although no difference between acupuncture and sham acupuncture was demonstrated, and clinical evidence on follow-ups is absent.

Our study will be a 4-month multi-center, randomized, sham-controlled clinical trial designed to evaluate the efficacy and safety of acupuncture for clinical symptomatic improvement of hand OA.

## Methods

### Study design

This multi-center, randomized, sham-controlled, participant-blinded and assessor-blinded trial will be carried out in six hospitals across Beijing, China. Patients with hand OA will be enrolled from April 2022 to October 2023. This clinical trial consists of a 4-week treatment period and a 3-month follow-up period. See study flowchart shown in Fig. 1.

**Fig. 1 Fig1:**
[figure not shown]
Schedule of enrolment, interventions, and assessments. VAS: Visual analog scale; AUSCAN: Australian Canadian Osteoarthritis Hand Index; FIHOA: Functional Index for hand OA; WHOQOL-BREF: World Health Organization Quality of Life abbreviated version

This trial will be conducted in accordance with the principles of the Declaration of Helsinki. The protocol has been approved by the Institutional Review Board of Guang’anmen Hospital, China Academy of Chinese Medical Sciences (ethical approval number: 2021-131-KY) on December 15, 2021. We developed this protocol conforming to the Standard Protocol Items: Recommendations for Interventional Trials (SPIRIT) checklist and the Standards for Reporting Interventions in Controlled Trials of Acupuncture (STRITCA). The registration number at www.clinicaltrials.gov is NCT05267093.

### Randomization and allocation

Eligible participants will be randomly assigned in a 1:1 ratio to either the traditional acupuncture group (TA) or the sham acupuncture group (SA). The randomization scheme will be generated by an independent institute, Lnkmed Tech Co. Ltd. (Beijing, China), and the allocation will be performed and concealed through the Interactive Web Response System (IWRS). Stratified permuted block randomization with center-based stratification and variable block size will be applied by Lnkmed using the SAS version 9.4. IWRS will assign a code to each enrolled participant, which will be concealed from participants, outcome assessors and the statisticians. The acupuncturist will be the only one who have access to both the code and the treatment labeled with the code.

### Blinding

In this study, the participants, outcome assessors, and the statisticians will be blinded to the group allocation. The acupuncturists will not be blinded due to the characteristics of acupuncture. Sham acupuncture treatment will mimic the similar sensation of traditional acupuncture treatment using blunt-tip needles. To ensure the success of blinding, the acupuncturists will be discouraged from discussing the treatments or expected results with participants. A blinding assessment will be taken right after the participant’s last session that asks the participant to guess which treatment he/she has received.

### Recruitment

This study plans to recruit 340 patients with hand OA from six hospitals across Beijing, China. Eligible patients who meet the American College of Rheumatology (ACR) diagnosis criteria of hand OA [23] in the dominant hand will be recruited via WeChat, websites, posters and bulletin boards in the hospitals and nearby communities. The rheumatologist of each center will be in charge of the diagnosis of participants. Informed consent will be adequately explained to all eligible participants. Participants will be asked to sign the consent form before screening, all of them have the right to withdraw their consent at any time and we guarantee the confidentiality of all participants.

### Inclusion and exclusion criteria

Participants who are diagnosed as hand OA in the dominant hand according to the ACR diagnosis criteria of hand OA [23] will be considered, specifically, hand pain or stiffness in the dominant hand with at least 3 of the following features: hard tissue enlargement of at least 2 of the 10 selected joints (the 2nd and 3rd distal interphalangeal (DIP) and proximal interphalangeal (PIP) joint and the first carpometacarpal (CMC) joint of both hands); hard tissue enlargement of at least two DIP joints; swelling of fewer than three metacarpophalangeal joints; deformity of at least one of the 10 aforementioned selected joints.

Participants who meet all of the following criteria might be included: (1) diagnosed as hand OA in the dominant hand; (2) history of hand OA for at least 3 months before enrollment and history of taking NSAIDs to treat hand OA; (3) aged 18–80 years; (4) scoring at least 40 mm in visual analog scale (VAS) for the average pain intensity over the last 48 h of the dominant hand, or an increase of ≥ 20 mm in VAS score after 1-week washout for participants applying NSAIDs at the enrollment; (5) Kellgren–Lawrence grade 1, 2, or 3 in symptomatic joints on posterior-anterior radiographs; (6) negative results in both rheumatoid factor and anticyclonic citrullinated peptide; (7) able to comply with the study protocol and understand the medical information forms; (8) voluntarily sign the informed consent.

Participants who meet any of the following criteria will be excluded: (1) history or current evidence of secondary OA, or symptomatic OA of other joints requiring treatment, or any upper limb pain that may interfere with the evaluation of hand pain; (2) history of inflammatory arthritis (such as rheumatoid arthritis and psoriatic arthritis), hemochromatosis, metabolic or neuropathic arthropathies; (3) history of trauma, dislocation or operation to the hand or arm within the previous 3 months; (4) hand pain and stiffness due to tissue scarring or tendinitis; (5) skin damage or serious skin disorder of the hands; (6) in the administration of antidepressants, anticonvulsants, vascular or narcotics within the previous 10 days; (7) oral, intramuscular, intra-articular or intravenous corticosteroids, or hyaluronic acid injection within 3 months; (8) uncontrolled dangerous conditions such as cancer, uncontrolled cardiovascular disorder, hepatic/renal insufficiency or coagulation disorder; (9) afraid of needles or received acupuncture treatments within 4 weeks.

### Interventions

#### TA group

In each center, treatments will be performed by a licensed acupuncturist who have at least 2 years of clinical experience. Before the study starts, the acupuncturists will be extensively trained on the location, depth and angle of acupuncture.

Acupoints are selected in accordance with the meridian theory of traditional Chinese medicine and the consensus of senior doctors, including bilateral Baxie (EX-UE9), bilateral Houxi (SI3), bilateral Waiguan (TE5) and Ashi points. All acupoints will be localized based on the World Health Organization (WHO) Standard Acupuncture Locations as exhibited in Table 1 and Fig. 2. The acupuncturist will first sterilize local skin with 75% alcohol cotton pellets and tape foam pads (Fig. 3), then insert sterile disposable needles (size 0.3 mm × 25 mm) into the acupoints and gently rotate and lift several times to obtain Qi (deqi) response. The depths and angles of needle insertion are shown in Table 1. Every treatment session will last for 30 min, and then, the needles will be gently removed by acupuncturists. Participants will receive three treatment sessions per week (every other day) for 4 consecutive weeks. Using a treatment diary, the treatment sessions will be monitored and assessed.

**Table 1 Tab1:** Locations and manipulations of acupoints

	Location	Depth	Anatomy	Deqi
Baxie (EX-UE9)	Proximal to the web margins between the five fingers at the junction of the red and white skin, 4 points on each hand, 8 in total	0.2–0.5 cun	Interossei muscles	Yes
Waiguan (TE5)	On the posterior aspect of the forearm, 2 cun^a^ proximal to the dorsal wrist crease, midpoint of the interosseous space between the radius and the ulna	0.5–0.8 cun	Between the extensor digitorum and the extensor hallucis longus	Yes
Houxi (SI3)	In the depression proximal to the ulnar side of the fifth metacarpophalangeal joint, at the junction of the red and white flesh	0.2–0.5 cun	Beside the origin of the abductor digiti minimi muscle of hand	Yes
Ashi points	At the midpoint of the dorsum of the most painful joint	0.1 cun	Subcutaneous	No

^a^From the cubital crease to the wrist crease: 12 cun

**Fig. 2 Fig2:**
[figure not shown]
Locations of acupoints. EX-UE9: Baxie; TE5: Waiguan; SI3: Houxi

**Fig. 3 Fig3:**
[figure not shown]
Illustration of acupuncture. **A**. traditional acupuncture; **B**. sham acupuncture; **C**. blunt tip

#### SA group

Sham acupuncture will be performed in SA group. The specially designed blunt-tip sham needles (size 0.3 mm × 25 mm) will be utilized to mimic the sensation of TA and confuse the participants to the most extent. Acupoints used in the SA group are the same as those in the TA group. After local skin sterilized, small foam pads will be taped on acupoints to cover up the manipulation of SA. The acupuncturist will insert blunt-tip needles through foam pads (Fig. 3), leave the needles on the surface of skin without penetration, then thrust and rotate the needles to produce the sensation of piercing. Blunt-tip sham needles will remain 30 min on skin, then gently removed. The treatment sessions and frequency will be the same as in TA group. The treatment diary will also be used in SA group.

### Rescue medication

Any other therapy will not be allowed during this trial, including oral medications (such as glucosamine sulfate, corticosteroids, and chondroitin sulfate) and topical agents (such as diclofenac sodium gel and ibuprofen gel). Acetaminophen (sustained release type, 500 mg/T) will be allowed to a maximum dose of 4 tablets daily for up to 3 days in total in case of insufferable pain. Rescue medicine should not be prescribed within 60 h before any of the assessments. Usage of rescue medication or other unexpected therapies will all be recorded in detail and properly analyzed.

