### Primary outcome

The primary outcome will be the proportion of responders at week 5. The proportion of responders at week 8 and week 16 will be assessed as secondary outcome. Participants will be defined as “responders” if showing at least 1 of the 3 following criteria: (1) at least a 50% decrease and absolute change from baseline ≥ 20 in visual analog scale (VAS) score on average pain intensity; (2) at least a 50% decrease and absolute change from baseline ≥ 20 in Australian Canadian Osteoarthritis Hand Index (AUSCAN); (3) at least a 20% decrease and absolute change from baseline ≥ 10 in at least two measurements of VAS score, AUSCAN and patient global assessment of improvement. The responder criteria are summarized by the Outcome Measures in Rheumatological Clinical Trials and Osteoarthritis Research Society International (OMERACT-OARSI) [24]. Responders are acknowledged to have clinically active treatment effect [25], since this assessment uses both a relative and an absolute change in three different domains (pain, function and patient’s global assessment) instead of single measurement.

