### Visual analog scale (VAS) for pain intensity

The VAS is a validated scale presented as a 100-mm line on paper, anchored by “no pain” at 0 and “worst imaginable pain” at 100. The participants will be asked to mark the line to estimate pain intensity of their dominant hand during the last 48 h. The VAS score will be measured from 0 to the participant’s mark, with a maximum score of 100 [26]. VAS scores can be categorized into four degrees: 0 (no pain), 1–34 (mild), 35–74 (moderate) and 75–100 (severe) [27]. A 15-point decrease from baseline is required to achieve Minimal Clinically Important Difference (MCID) for patients with hand OA [28]. The change in VAS score from baseline on average pain intensity and maximum pain intensity and the proportion of participants achieved MCID on average pain intensity will be measured at baseline, week 5, week 8, and week 16.

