### Australian Canadian Osteoarthritis Hand Index (AUSCAN)

The AUSCAN index is designed as a self-administered questionnaire for the evaluation of both pain and physical function in hand OA. VAS scaling is presented to the participants for the measurement of pain intensity (during 5 types of activity), stiffness (in the morning), and physical function (during 9 types of activity) [29]. By presenting as a 100-mm line, verbal descriptor “no pain/no stiffness/no difficulty” is anchored on 0 mm and “the most imaginable pain/ the most imaginable stiffness/ the most imaginable difficulty” is anchored on 100 mm for the 3 dimensions. The AUSCAN subscale scores will be calculated as the average of scores within each dimension. Higher scores indicate worse condition [30]. The AUSCAN total score will be the average of scores on the 15 items above. It is a reliable and responsive self-reported measurement that eliminates observer variation. Participant will be asked to complete the AUSCAN to indicate the condition of the dominant hand during the previous 48 h at baseline, week 5, week 8, and week 16.

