### Patient global assessment

The participants’ assessment of their global status of the dominant hands during the last 48 h will be measured using a VAS (0 represents “worst possible”, 100 represents “best possible”) [34] at baseline, week 5, week 8, and week 16. Patient global assessment has been recommended as a core outcome domain of clinical trials in hand OA.

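### The 60 h rescue rule limits prescribing rather than taking, so read literally it does not guarantee a 48 h recall free of rescue acetaminophen

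*Protocol article*

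**What the plan says.** Under Rescue medication, the protocol article bars other therapies and permits one rescue drug, sustained-release acetaminophen in 500 mg tablets, for unbearable pain. It "will be allowed to a maximum dose of 4 tablets daily for up to 3 days in total". The timing rule follows: "Rescue medicine should not be prescribed within 60 h before any of the assessments". The section then adds: "Usage of rescue medication or other unexpected therapies will all be recorded in detail and properly analyzed". The Other outcomes row of Table 2 lists how many participants use rescue, how often, and the total dose.

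The Primary outcome section builds the week-5 responder from three measures. A large enough improvement in VAS pain alone or in AUSCAN alone qualifies, as does a smaller one "in at least two measurements of VAS score, AUSCAN and patient global assessment of improvement". Each measure has a 48 h recall:

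- VAS pain: participants "mark the line to estimate pain intensity of their dominant hand during the last 48 h".
- AUSCAN: completed "to indicate the condition of the dominant hand during the previous 48 h".
- Patient global assessment: "global status of the dominant hands during the last 48 h will be measured using a VAS".

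**The concern.** A pre-visit rescue limit is there to keep analgesic intake out of the period that participants are asked to rate. Here the limit attaches to the prescription, while the permitted use can extend over days. Prescription and last tablet can therefore be far enough apart for a site to follow the sentence exactly and still have acetaminophen taken inside the recall, with no protocol deviation to record.

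All three responder components are self-reports over the same 48 h, so an overlap would affect every route to being counted a responder. The rule governs all assessments, so the same holds for the secondary responder outcomes at weeks 8 and 16.

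**Working it through.** **Inputs.** From Rescue medication: limit 60 h, on prescribing; at most 4 tablets of 500 mg a day; at most 3 days. From the VAS, AUSCAN and Patient global assessment sections: recall 48 h.

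**Where 60 h may come from.** The article does not explain the figure. 60 − 48 = 12, so it equals the recall plus a 12 h margin. That makes sense if the limit is on intake.

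**Literal reading.** Let the prescription fall t hours before the visit, with t at least 60. Assume that intake starts at prescription and runs without a break for L hours. Intake then covers the period from t to t − L hours before the visit, and

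overlap = max(0, 48 − max(t − L, 0)).

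There is no overlap once t is at least 48 + L.

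| Course | Overlap at t = 60 | Smallest t with no overlap | Shortfall of the 60 h limit |
|---|---|---|---|
| 12 h or less | 48 − 48 = 0 h (at L = 12) | 48 + 12 = 60 h | none |
| 1 day (24 h) | 48 − 36 = 12 h | 48 + 24 = 72 h | 12 h |
| 2 days (48 h) | 48 − 12 = 36 h | 48 + 48 = 96 h | 36 h |
| 3 days (72 h) | 48 − 0 = 48 h | 48 + 72 = 120 h | 60 h |

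For the 3-day course, the overlap stays at 48 h for t from 60 to 72, then falls as 120 − t: 36 h at 84, 24 h at 96, 12 h at 108, and 0 h from 120.

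**Tablets in the worst case.** At the maximum dose, 48/24 × 4 = 8 tablets (8 × 500 = 4,000 mg) fall inside the recall, out of 3 × 4 = 12 permitted (6,000 mg).

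**Delayed intake.** If tablets are kept, a single tablet prescribed at 60 h and held for 12 h is taken 60 − 12 = 48 h before the visit, at the edge of the recall; held longer, it falls inside. No limit on prescribing alone excludes this.

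**Intake reading.** If the last permitted tablet is at 60 h, it precedes the opening of the recall by 60 − 48 = 12 h. Overlap is zero for every course length.

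**The case against.** The strongest reply is that the verb is merely loose and that any site would understand it as a limit on taking. The 12 h margin supports this, and so does the next sentence of the section, which speaks of usage. The inclusion criteria also refer to use, in the pain threshold "after 1-week washout for participants applying NSAIDs at the enrollment", though that concerns another drug at another time and is weak support. On the intake reading the recall is fully protected. This probably is the intent. It does not make the sentence say so, and six hospitals have to apply it.

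Second, the overlaps are conditional. They need a prescription between 60 h and just under 120 h before a visit, an immediate start and consecutive days; the tablet count also needs the maximum dose. The 3 days are a cumulative ceiling, not a prescribed 72 h course, and use is confined to unbearable pain. All of this stands and limits the exposure.

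Third, rescue use is recorded and reported, so an imbalance in overall use between the groups would be visible. That also stands, although the listed measures do not place intake in relation to visits.

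Fourth, this is a journal article, and the full protocol may tell participants when tablets may be taken. That could resolve the point in practice; the published sentence would still need correcting.

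A reader might go further and infer that the rule fails for every permitted course. It does not: brief use at once and courses prescribed early enough and taken promptly stay clear. Nor does the text show that the design chose to leave intake unrestricted.

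**Conclusion.** The point holds as a minor wording defect in a conduct rule. Read literally, the rule does not guarantee that the 48 h recall is free of rescue analgesic. The overlap is about 12, 36 or 48 h for a 1-, 2- or 3-day course prescribed at the 60 h limit, assuming an immediate start and unbroken intake. It is zero for use of 12 h or less taken at once, and for courses prescribed at least 72, 96 or 120 h before and started at once.

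A reader might also infer that the primary comparison is biased. The documents do not support that. They give no rescue rate and nothing on how use would differ between the groups; the same rule applies to both, and participants and outcome assessors are blinded. Neither the size nor the direction of any bias can be stated. The sample size is unaffected.

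**What to change.** In the timing sentence under Rescue medication, replace the word prescribed with taken, and tell the sites that the limit applies to intake. The 60 h figure, the daily dose and the 3-day ceiling can stay.

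Lengthening the interval while keeping the limit on prescribing is the poorer choice. It would need 120 h to cover a 3-day course started at once, and would still not cover tablets kept for later.

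The cost is one word and a note to sites, with no change to data capture, sample size or analysis.
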